## Sample size

For sample size and power calculation, we made the following assumptions:

- Minimally important difference in questionnaire score of 10% change due to the intervention.
- Standard deviation of change in score of 40%.
- A drop-out rate of about 20% due to factoring including movement of subjects out of the area.

A sample size of 504 subjects (252 subjects in each group) will provide a power of 80% to detect a change in questionnaire score by t-test with a two-sided type I error of 0.05. Considering the drop-out rate, we proposed to recruit a total of 600 subjects (300 in each group).

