# RANDOMIZATION

In this randomized control trial, eligible students will be randomized by block randomization, as explained below. The students will be assigned a study ID number through sorting their last names (and first names if necessary) alphabetically and then assigned a study ID number. They will then be partitioned by simple randomization of their subject ID number within their classrooms using STATA software to either receive a one-hour script-based teaching on either the effects of air pollution on lung health (intervention group) or the role of vaccination in public health (control group), such that about equal numbers of students in each classroom were assigned to intervention and control groups.

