## Statistical Models

- Paired t-test comparison of pre versus post teaching session.
- Linear regression modeling analysis will be performed to compare the scores and change in them between the intervention and control group with adjustment for covariates including age, sex, race, ethnicity, income level, and assigned classrooms as appropriate.
- Multivariate generalized estimating equation regression analysis will be performed to determine whether there is an incremental effect from “time” on scores and change in scores with adjustment for covariates including age, sex, race, ethnicity, income level, and assigned classrooms as appropriate.

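### The 80% power assumes independent students, and the stated models have no term for the teaching session that students share after randomisation

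*Protocol*

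**What the plan says.** Section 13.1 of the protocol lists its assumptions: "Minimally important difference in questionnaire score of 10% change due to the intervention", "Standard deviation of change in score of 40"%, and a comparison "by t-test with a two-sided type I error of 0.05". From these it concludes: "A sample size of 504 subjects (252 subjects in each group) will provide a power of 80% to detect a change in questionnaire score". It mentions no ICC, session size, number of sessions or design effect.

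Under Randomization, students are "partitioned by simple randomization of their subject ID number within their classrooms using STATA software to either receive a one-hour script-based teaching", with roughly equal numbers going to each arm in every classroom. The Overview of the study design describes the teaching as classroom-based and interactive. The Teaching session section adds that it follows a script and a slide set.

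Section 13.4 plans a linear regression comparing the arms with "adjustment for covariates including age, sex, race, ethnicity, income level, and assigned classrooms as appropriate". It also plans a generalized estimating equation (GEE) model, described as examining the effect of time, without saying what its clusters are. Neither model names the teaching session, and session attended is not among the listed variables or covariates.

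**The concern.** Randomising individuals makes the arms comparable at the start, but the intervention is then delivered to groups. Students in one session share a presenter, a room, a discussion and a set of peers. Anything that makes one session work better than another moves all its students together, so their outcomes can be correlated even though their allocations were independent.

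A classroom main effect does not deal with this. It takes out what the two halves of a classroom have in common. The session effect belongs to one half only, so it enters the difference between arms directly.

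Two things are at stake for the primary behaviour-score comparison. The power of a valid test may be lower than stated. And a test whose standard error ignores the session would reject a true null hypothesis more than 5% of the time.

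**Working it through.** **1. The protocol's own figure.** The inputs from Section 13.1 are difference 10, SD 40 (standardised difference 0.25), two-sided alpha 0.05 and power 80%.

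n per group = 2 × (1.960 + 0.842)² × 40² / 10² = 251.2, rounded up to 252. The two-sample t-test at 252 per group has power 79.98%. The figure therefore reproduces with a design effect of exactly 1.

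**2. Power with a session correlation.** Let m be the analysed students per session and ρ the session ICC of the change score, equal in both arms. Both are assumptions.

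Design effect DE = 1 + (m − 1)ρ, and effective n per group = 252 / DE.

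| m | ρ | DE | Effective n per group | Power |
|---|---|---|---|---|
| 12 | 0 | 1.00 | 252 | 80.0% |
| 12 | 0.01 | 1.11 | 227.0 | 75.7% |
| 12 | 0.02 | 1.22 | 206.6 | 71.7% |
| 12 | 0.05 | 1.55 | 162.6 | 61.3% |
| 25 | 0.01 | 1.24 | 203.2 | 71.0% |
| 25 | 0.02 | 1.48 | 170.3 | 63.3% |
| 25 | 0.05 | 2.20 | 114.5 | 47.0% |

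These are powers for a test that allows correctly for the session. They keep the full SD of 40 and give no credit for classroom adjustment.

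**3. Crediting the classroom adjustment.** Let c be the classroom ICC (also assumed), removed by within-classroom randomisation and the covariate. For m = 12 the variance factor becomes (1 − c − ρ) + 12ρ.

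| c | ρ | Factor | Power |
|---|---|---|---|
| 0.05 | 0.005 | 1.005 | 79.8% |
| 0.10 | 0.005 | 0.955 | 81.8% |
| 0.10 | 0.01 | 1.01 | 79.6% |
| 0.10 | 0.02 | 1.12 | 75.4% |

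With c of 0.05 to 0.10 and no session effect, power would be about 82% to 84%. A small session ICC can thus be fully offset, while at 0.02 a loss remains.

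**4. Type I error if the session is ignored.** Assume 20 classrooms with two sessions of 12 each (480 students), classroom fixed effects and ordinary least-squares standard errors. On a scale where the variance left after removing classrooms is 1, the true variance factor for the contrast is v = (1 − ρ) + 12ρ. The residual mean square that the model uses has expectation [440(1 − ρ) + 19v] / 459.

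For ρ = 0.02: v = 1.22, the residual mean square is (431.2 + 23.18) / 459 = 0.990, and their ratio is 1.23. The true size is 2 × [1 − Φ(1.960 / √1.23)] = 7.7%.

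| ρ | Ratio | True size of a nominal 5% test | Simulated |
|---|---|---|---|
| 0.01 | 1.12 | 6.4% | 6.5% to 6.8% |
| 0.02 | 1.23 | 7.7% | 7.4% to 7.8% |
| 0.05 | 1.59 | 12.0% | 12.1% to 13.6% |

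The classroom adjustment is already in these figures, so it does not cure the problem.

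**The case against.** The strongest reply has four parts.

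- **The variance estimator is not fixed.** The protocol mentions no confidence intervals and names no method for standard errors, and the GEE's cluster unit is open. A session-robust variance would be compatible with the text and could be specified in the SAP, which is not shown. This stands. A reader might infer that the trial's intervals will be too narrow, but the document does not establish that. The type I figures describe an ordinary least-squares analysis, which the text permits but does not prescribe.
- **Classroom clustering is handled.** A reader might infer that the trial needs the design effect of a cluster-randomised trial. It does not: allocation is within classroom and the models adjust for classroom, so variation common to both arms cancels. Only the session component remains.
- **Lower power is not inevitable.** A reader might infer that any positive session correlation puts power below 80%. Step 3 of the working shows otherwise when the classroom ICC is sizeable and the session ICC very small. Adjustment for the other covariates could help too.
- **The session ICC may be negligible.** Delivery follows a script and fixed slides, the session lasts one hour, and outcomes run to twelve months. The number of presenters and sessions is not given. All this is fair, but a script does not remove peer discussion in an interactive session, and nothing in the protocol shows that the correlation is zero.

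None of this alters two facts: the stated power includes no allowance for shared sessions, and the classroom covariate cannot supply one.

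**Conclusion.** The point holds in a limited form. It is certain that 252 per group gives 80% power only with independent students, and that no stated model has a session term. How much this matters cannot be determined from the protocol.

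Under the assumed 12 students per session and session ICC of 0.01, 0.02 or 0.05, power is about 76%, 72% or 61% before crediting classroom adjustment. If ordinary standard errors are used with classroom fixed effects, type I error is about 6-7%, 8% or 12%. Larger sessions make both worse. A session ICC of 0 leaves the plan's figures intact, and one of about 0.01 may be nearly offset by removing classroom variance.

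The protocol's arithmetic on its own assumptions is correct. The gap is an unstated assumption and an unnamed source of correlation. It should be corrected because the remedy is cheap and depends on session attendance having been recorded.

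**What to change.** 1. Record for each student which teaching session was attended.
2. In Section 13.4, fit the between-arm models with a random effect for session, or with session-level cluster-robust standard errors and a small-sample correction. Keep classroom as a covariate. State the cluster unit of the GEE so that it also allows for the session.
3. In Section 13.1, say that 80% power assumes no correlation within teaching sessions. Give the expected session size and number of sessions per arm, and report power over a small range of session ICCs, for example 0 to 0.05, with and without credit for classroom adjustment.

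The cost is one recorded variable and some analysis wording. If the session correlation is positive, intervals become slightly wider and the stated power slightly lower. No extra students are required.

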## Exclusion criteria

1. Learning disabilities (such as autism).
2. Moving out of the area within the next 6 months
3. Inability to complete pre-intervention questionnaire.

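### The recruitment target of 600 covers 16% drop-out, not the 20% that the protocol assumes; at 20% loss, 480 students remain and power is about 78%

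*Protocol*

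**What the plan says.** Section 13.1 (Sample size) of the protocol lists three assumptions:

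- "Minimally important difference in questionnaire score of 10% change due to the intervention"
- "Standard deviation of change in score of 40" per cent
- "A drop-out rate of about 20% due to factoring including movement of subjects out of the area"

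It then gives the requirement, "A sample size of 504 subjects (252 subjects in each group"), which "will provide a power of 80% to detect a change in questionnaire score" "by t-test with a two-sided type I error of 0.05". The recruitment target follows: "Considering the drop-out rate, we proposed to recruit a total of 600 subjects (300 in each group").

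The synopsis (Section 2, Rationale for Number of Subjects) repeats the 504 and the 600 and refers to drop-out, but gives no rate. The synopsis row for the number of subjects also gives 600.

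**The concern.** The protocol presents 600 as the number reached once drop-out has been taken into account. A recruitment target does that if the students left after the assumed loss are at least as many as the analysis needs. Here the assumed loss, the number needed and the target stand in one short section, and they do not fit together: 20% of 600 is 120, which leaves 480 and not 504.

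The size of the trial is justified by this one passage. A reader will take it to mean that 80% power is protected against the expected loss, and on the protocol's own figures it is not quite protected. The mismatch lies wholly within the protocol's stated inputs and result, so it does not depend on any detail that a statistical analysis plan might add.

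**Working it through.** **Inputs, all from Section 13.1:** difference 10%, SD of change 40% (standardised effect 10/40 = 0.25), two-sided type I error 0.05, power 80%, equal groups, drop-out about 20%, 504 required, 600 recruited.

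**1. Reproduce the requirement.** For two independent means, by the normal approximation:

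n per group = 2 × (1.960 + 0.842)² × (40/10)² = 2 × 7.849 × 16 = 251.2, rounded up to 252, so 504 in total.

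This matches the protocol exactly. The noncentral t gives 253 per group, and power of 0.800 at 252. The 504 is sound.

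**2. Inflate for drop-out.** If a fraction d is lost, the number to recruit is N/(1 − d):

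504/(1 − 0.20) = 630 (315 per group).

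The stated 600 is 30 below this, or 30/630 = 4.8%.

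**3. Work back from 600.**

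- Students left at 20% loss: 600 × 0.80 = 480 (240 per group), which is 504 − 480 = 24 short.
- Largest loss that still leaves 504: 1 − 504/600 = 16.0%.

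**4. Power at 240 per group.**

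- Normal approximation: 0.25 × √(240/2) − 1.960 = 2.739 − 1.960 = 0.779, so power is 78.2%.
- Noncentral t: 78.0%.
- Difference detectable with 80% power (noncentral t): 0.2563 SD × 40% = 10.25%, against the planned 10%.

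**5. Allow for the word about.**

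| Drop-out | Left from 600 | Recruits needed for 504 | Power with 600 recruited (noncentral t) |
|---|---|---|---|
| 15% | 510 | 593 | 80.4% |
| 16% | 504 | 600 | 80.0% |
| 18% | 492 | 615 | 79.0% |
| 20% | 480 | 630 | 78.0% |
| 22% | 468 | 647 | 77.0% |

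No rate that rounds to 20% makes 600 sufficient.

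**6. Possible origin of the 600.** Multiplying by 1 + d instead of dividing by 1 − d gives 504 × 1.20 = 604.8, which is close to 600. That is a plausible source, but the protocol does not show the step, and plain rounding could explain the figure as well.

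**The case against.** The strongest reply is that this hardly matters. The loss is about 2 points of power, the detectable difference moves by a quarter of a percentage point, and the drop-out rate is given only as approximate. This stands as to size and sets the weight of the point. It does not remove the error, because 600 is enough only at 16% or below.

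A second reply is that 78% is the power of an unadjusted t-test, whereas Section 13.4 plans covariate-adjusted linear regression and generalised estimating equations over repeated surveys. Adjustment could recover the loss. As an illustration only, since the protocol gives no correlation: if the covariates correlated 0.2 with the change score, power at 240 per group would be about 79.7%, and at 0.3 about 81.7%. This is fair, and it means that 78% is not a forecast for the planned regression. But Section 13.1 sizes the trial by a simple t-test and claims no such gain, so its arithmetic has to be judged on that basis.

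A reader might also be tempted by three stronger readings that the protocol does not support.

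- *That the 80% power statement is false.* The protocol attaches 80% to 504 students, and that is correct. The fault is in the step from 504 to 600.
- *That the shortfall falls on the 12-month survey.* Section 13.1 ties the 20% to no visit, and Section 8.1 gives the primary outcome no time point. The survey is also given immediately after teaching and at about 3 and 6 months, and a student lost later still contributes to the earlier comparisons. The overview speaks of long-term efficacy, but nothing makes 12 months the powered comparison.
- *That the exclusion "Moving out of the area within the next 6 months" is too short for a 12-month study and should be lengthened.* Students who move later are part of what a drop-out allowance is for, so that criterion contradicts nothing. Moving is named as one example of a cause, with no share given, so the benefit of a longer limit cannot be estimated. It would be a separate eligibility trade-off and is not needed to correct the arithmetic.

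**Conclusion.** The recruitment target does not follow from the protocol's own drop-out assumption. At 20% loss, 600 leaves 480 students against the 504 required, with power of about 78% (78.0% by the noncentral t, 78.2% by the normal approximation) in place of 80%. The target covers a loss of 16%.

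This takes the 10% difference, the SD of 40% and the simple two-group t-test as the protocol states them, assumes equal loss in the two groups, and counts no gain from covariates or repeated measures. It is a small but real error in a figure on which the sample-size justification rests. It does not show a seriously underpowered trial.

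**What to change.** Keep 600 and correct the sentence in Section 13.1 and in the synopsis (Section 2, Rationale for Number of Subjects), in one of two ways:

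- with 20% drop-out, 480 subjects (240 per group) remain, giving about 78% power; or
- recruiting 600 allows for up to 16% drop-out, leaving 504.

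The first is the simpler, because it leaves the drop-out assumption as it stands. If the second is chosen, the rate of about 20% in the list of assumptions in Section 13.1 must be changed to agree, or the contradiction remains.

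The cost is one sentence in two places and a slightly less favourable stated figure. Recruitment, eligibility and analysis do not change. Raising the target to 630 would also make the figures agree, but it means 30 more students for about 2 points of power, and correcting the statement does not require it.

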## Measured variables.

### Independent variable

- One hour teaching session about air pollution and climate change

### Dependent Variables

- Behavior domain score (primary outcome).
- Total domain score (secondary outcome).
- Understanding domain score (secondary outcome)

## Covariates

- Age
- Sex
- Income level
- Race
- Ethnicity
- Assigned classrooms.

## Statistical Models

- Paired t-test comparison of pre versus post teaching session.
- Linear regression modeling analysis will be performed to compare the scores and change in them between the intervention and control group with adjustment for covariates including age, sex, race, ethnicity, income level, and assigned classrooms as appropriate.
- Multivariate generalized estimating equation regression analysis will be performed to determine whether there is an incremental effect from “time” on scores and change in scores with adjustment for covariates including age, sex, race, ethnicity, income level, and assigned classrooms as appropriate.

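### The covariate list for the between-arm regression leaves out the pre-teaching score, which costs precision but does not cause bias

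*Protocol*

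**What the plan says.** Section 8.1 makes the behavior domain score the primary outcome. Section 12.2 has students complete the questionnaire immediately before teaching, immediately after it, and at about three, six and twelve months. Section 9.5 excludes a student for "Inability to complete pre-intervention questionnaire".

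Section 13.3 lists six covariates: age, sex, income level, race, ethnicity and "Assigned classrooms". Section 13.4 plans a linear regression that will "compare the scores and change in them between the intervention and control group with adjustment for covariates including age, sex, race, ethnicity, income level"; classroom is also listed, with a qualifier that adjustment is made where appropriate. The GEE model for the effect of time carries the same six covariates and the same qualifier. The pre-teaching score is not named as a covariate anywhere. It enters the analysis through the paired pre/post t-test and through change as one of two regression outcomes.

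Section 13.1 sizes the trial on a "Minimally important difference in questionnaire score of 10% change due to the intervention" and a "Standard deviation of change in score of 40"%. Section 10 randomises students within classrooms.

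**The concern.** A student's earlier score on the same instrument is usually among the best predictors of the later one. Here it is measured before the arms diverge and is already collected. Leaving it out gives up precision that would cost nothing to obtain.

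Section 13.4 also plans both score and change as outcomes and does not say which form is the main comparison. With the baseline score in the model that choice stops mattering. Change is follow-up minus baseline, so switching the outcome moves the baseline coefficient by exactly 1 and leaves the arm coefficient untouched.

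Classroom is the randomisation stratum. It is on the list, but the qualifier makes its inclusion optional.

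**Working it through.** **Inputs from section 13.1.** Difference 10%; SD of change 40%; test "by t-test with a two-sided type I error of 0.05"; 80% power; drop-out about 20%; 600 recruited. **Assumed:** rho of 0.3, 0.5 or 0.7, equal pre and post variances, and a linear relation between pre and post scores. The protocol gives none of these.

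**1. Reproduce the plan's figure.** n per arm = 2 × (1.960 + 0.842)² × 40² / 10² = 251.2, rounded up to 252, or 504 in total. This matches "A sample size of 504 subjects (252 subjects in each group"). Power at 252 per arm is 80.1%.

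**2. Numbers after drop-out.** 600 × 0.80 = 480, or 240 per arm. The standard error for change is 40 × sqrt(2/240) = 3.65. Then 10/3.65 - 1.96 = 0.78, which is power of 78.2%.

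**3. Variances.** With score variance s²:
- follow-up score: s²
- change: 2s²(1-rho)
- follow-up score adjusted for baseline: s²(1-rho²)

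Adjusted over change is (1-rho²)/[2(1-rho)] = (1+rho)/2. Adjusted over score is 1-rho². Both ratios are below 1 for any rho strictly between 0 and 1.

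**4. Illustration.** Hold the SD of change at 40%. The score SD is then 40/sqrt(2(1-rho)) and the adjusted SD is 40 × sqrt((1+rho)/2).

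| rho | Adjusted SD | Variance cut against change | Variance cut against score | n per arm for 80% power, adjusted | Power at 240 per arm: change | Score | Adjusted |
|---|---|---|---|---|---|---|---|
| 0.3 | 32.2 | 35% | 9% | 164 | 78.2% | 90.0% | 92.5% |
| 0.5 | 34.6 | 25% | 25% | 189 | 78.2% | 78.2% | 88.5% |
| 0.7 | 36.9 | 15% | 49% | 214 | 78.2% | 56.4% | 84.4% |

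These powers use the normal approximation. With the t distribution they are slightly lower: 78.0% for change, and 92.4%, 88.4% and 84.2% adjusted.

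**5. Limit on recovering the drop-out shortfall.** A 20% loss would need 504/0.80 = 630 recruits, not 600. Adjustment makes up the difference only if (1+rho)/2 is at most 240/252 = 0.952, that is, rho up to about 0.90.

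**The case against.** **The list is open-ended and a statistical analysis plan may exist.** The wording of section 13.4 would permit a baseline term, and final covariates are often settled in the analysis plan. That is fair, but section 13.3 is a plain list without the term. Permitting a covariate is not the same as planning it.

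**Nothing planned is invalid.** This stands in full. A reader might infer that the treatment estimate is biased by regression to the mean or by chance baseline imbalance. The documents do not support that. Under randomisation, regression to the mean acts on both arms alike, and chance imbalance averages out over randomisations. The loss is one of efficiency.

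**The planned models are already adjusted.** This also stands. A reader might take the plan to compare raw scores and raw changes, but both models carry six covariates. If those covariates share information with the baseline score, the net gain is smaller than the table shows.

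**The percentages are hard to place on this instrument.** Section 13.1 does not say what 40% is a percentage of. If it is the 28-point behavior range (10 to 38), rho of 0.7 implies a score SD of 51.6% of range, above the 50% maximum that any bounded score can have. Under that reading, the rho 0.7 row cannot occur. The variance ratios in step 3 do not depend on the scale, so they hold; the powers are illustrative only.

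**Complete baseline data are not guaranteed.** The exclusion covers inability to complete the questionnaire; it does not ensure that every item is answered. Baseline scores should be nearly complete, and a few may be missing.

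**Baseline cannot simply be added to both models.** Correct. If the pre-teaching score is one of the repeated responses in the GEE model, entering it as a covariate too would put it on both sides.

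**Conclusion.** The point holds as a matter of precision. Sections 13.3 and 13.4 set out a covariate list without the baseline domain score, and for any rho strictly between 0 and 1 both planned forms of the comparison are less precise than the adjusted one. On the plan's own SD of change and 240 per arm, power rises from about 78% for change to about 92%, 88% and 84% at rho 0.3, 0.5 and 0.7. Those figures rest on an assumed rho, equal variances, linearity, and no allowance for what the listed covariates already explain.

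Two further inferences go too far. Baseline adjustment does not make up the recruitment shortfall unconditionally; that fails above a rho of about 0.90, and possibly sooner once the other covariates are counted. Nor does it settle everything about the main comparison: it removes the choice between score and change, but not the choice of follow-up visit.

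The change is worth making because the data are already collected. Without it the randomised comparison remains sound.

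**What to change.** - **Section 13.3:** add the pre-teaching score of the domain being analysed (behavior, understanding or total).
- **Section 13.4, linear regression:** model the follow-up score on arm, baseline score and classroom, with any other listed covariates fixed in advance. Always include classroom, because randomisation is within classroom.
- **Section 13.4, GEE model:** choose one of two forms and state it. Either use only post-teaching scores as responses, with the baseline score as a covariate, or keep the pre-teaching score as a response and do not also enter it as a covariate.

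The cost is protocol wording only. No new data, visits or students are needed.

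### The regression models in section 13.4 leave out the pre-teaching score, which costs precision, and unweighted GEE with about 20% drop-out may bias the 12-month arm difference; a baseline-adjusted likelihood model is a better choice at little cost

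*Protocol*

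**What the plan says.** Protocol section 13.4 lists three analyses. The first is a paired t-test before and after teaching. The second makes the comparison between arms: "Linear regression modeling analysis will be performed to compare the scores and change in them between the intervention and control group". The third is longitudinal: "Multivariate generalized estimating equation regression analysis will be performed to determine whether there is an incremental effect", the effect in question being that of time, on scores and on change in scores. Both regressions are to be fitted "with adjustment for covariates including age, sex, race, ethnicity, income level, and assigned classrooms as appropriate".

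Section 13.3 names the same six covariates as a plain list. The pre-teaching score is in neither place. It is available, however: section 12.2 has the questionnaire completed at Visit 1 just before teaching, and section 9.5 excludes students who cannot complete it.

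On losses, section 13.1 assumes "A drop-out rate of about 20% due to factoring including movement of subjects out of the area". Section 7.1 gives long-term efficacy in a repeated-measures design as the interest, and section 12.2 places the last survey at about twelve months.

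**The concern.** Two things follow from the models as stated.

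First, the earlier measurement of the same questionnaire is normally the strongest predictor of the later one. Leaving it out of the covariates discards information that the trial already holds on every student, and this loss does not depend on who drops out.

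Second, ordinary unweighted GEE is in general guaranteed consistent only when missingness does not depend on observed outcomes, given the covariates in the model. A likelihood-based repeated-measures model uses the same observed surveys and remains valid when missingness depends on observed earlier scores. The 12-month arm difference is where the trial's interest lies and where cumulative loss is greatest. Students know which lesson they had (section 11), so loss that differs by arm is possible, though the protocol does not say that it will occur.

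**Working it through.** **The plan's own figure.** Section 13.1 gives "Minimally important difference in questionnaire score of 10% change due to the intervention" and an SD of change of 40%, so the standardised difference is 10/40 = 0.25. Per arm, n = 2 × (1.960 + 0.842)² × (40/10)² = 2 × 7.85 × 16 = 251.2, rounded up to 252, or 504 in all. The stated evaluable number reproduces.

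The simulations below take 0.25 SD as the true 12-month effect, in units of the SD of a single score. The plan's 0.25 is in units of the SD of change. The two coincide when the correlation is 0.5, since √[2(1 − 0.5)] = 1.

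**Precision without informative drop-out.** Let the score SD be 1 and ρ the correlation between the pre-teaching and 12-month scores. With 600 students and 20% lost, 240 per arm remain. The standard errors of the arm difference are:

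- raw score: √(2/240) = 0.091
- change score: 0.091 × √[2(1 − ρ)]
- score adjusted for baseline: 0.091 × √(1 − ρ²)

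| Assumed ρ | Raw | Change | Adjusted |
|---|---|---|---|
| 0.6 | 0.091 | 0.082 | 0.073 |
| 0.8⁴ = 0.41 | 0.091 | 0.099 | 0.083 |

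The variance falls by ρ² against the raw score (36% and 17%). Against change the variance ratio is (1 + ρ)/2, a fall of 20% and 30%. Adjustment is therefore never worse than either.

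Simulation with data missing completely at random (200 runs, about 20% missing at month 12) gave these SDs of the estimate:

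- ρ = 0.6: 0.084-0.091 for GEE on score, 0.084-0.086 for GEE on change, 0.074 for the likelihood model with baseline.
- ρ = 0.41: 0.091-0.094, 0.108-0.113 and 0.089 respectively.

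An SD from 200 runs carries about 1/√400 = 5% error. At ρ = 0.41 the change and adjusted values lie above the formula (0.113 against 0.099 is 14%), and the gain over raw scores is small there. The ordering is the same. Much of the gain comes from the covariate rather than the likelihood method: at ρ = 0.6, GEE with baseline gave 0.073-0.075.

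**Bias under score-driven drop-out.** Two simulations were run, each with 600 students, a true 12-month effect of 0.25 SD, about 20% lost by month 12 and 200 runs (simulation error about 0.006).

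- *A*: correlation 0.4 + 0.4·exp(−Δt/6) for surveys Δt months apart; loss depends on the last observed score in the intervention arm only.
- *B*: correlation 0.6 throughout, or 0.8 to the power of the number of surveys apart. Loss depends on the last score in the control arm only (logit −2.9 − score, against a constant −2.56 in the intervention arm), or by the same rule in both arms (logit −2.75 − score).

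Bias in the 12-month arm difference, in SD:

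| Method | A, one arm | B, one arm (0.6 / 0.8ᵏ) | B, same rule (0.6 / 0.8ᵏ) |
|---|---|---|---|
| GEE independence, score | +0.101 | −0.121 / −0.118 | −0.039 / −0.017 |
| GEE exchangeable, score | −0.010 | −0.002 / +0.014 | −0.005 / +0.016 |
| GEE independence, change | not run | +0.004 / 0.000 | +0.008 / +0.008 |
| GEE exchangeable, change | not run | +0.033 / +0.038 | +0.017 / +0.018 |
| GEE independence + baseline | +0.019 | −0.046 / −0.072 | −0.011 / −0.008 |
| GEE exchangeable + baseline | −0.020 | +0.002 / −0.012 | +0.003 / +0.006 |
| Likelihood, unstructured + baseline | 0.000 | +0.003 / +0.004 | +0.004 / +0.011 |

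With the same rule in both arms, simulation A gave 0.239 for all five methods that it compared, within two simulation errors of 0.25. The largest biases are 0.101/0.25 = 40% and 0.121/0.25 = 48% of the assumed effect. Their sign follows the arm in which low scorers leave.

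With a separate arm effect at each visit, as in B, independence GEE gives the same point estimate as a linear regression fitted survey by survey to the students present. The independence rows therefore also bear on the linear regression bullet, if it is fitted that way.

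**The case against.** The strongest reply is that GEE for repeated surveys is a recognised method and that the protocol misstates nothing by naming it. Several parts of this reply stand.

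- A reader might infer that GEE requires data missing completely at random, so that the 12-month result will be biased. That is too absolute. Weighted GEE, or GEE after multiple imputation, can handle loss that depends on observed scores. Exchangeable GEE on scores was within about 0.016 SD of the truth throughout. The protocol excludes none of these. Working correlation, weighting and imputation are ordinary content of a statistical analysis plan, which is not shown, so their absence is no fault here.
- A reader might infer that nothing in the models carries the baseline. That is also too strong. Change in score is one of the modelled outcomes, and the list in 13.4 is worded openly: "adjustment for covariates including age, sex, race, ethnicity, income level, and assigned classrooms as appropriate". But change fixes the baseline slope at one instead of estimating it, which costs precision, and the list in 13.3 has no such opening.
- GEE is named for the effect of time, while linear regression compares the arms. Replacing only the GEE bullet would miss the stated comparison. This is correct, and it is why the fix covers both bullets.
- Score-driven loss in one arm only is conjecture. Section 13.1 names moving away as a cause, and nothing in the protocol says that loss will follow earlier answers. The bias figure is therefore conditional.
- Adding baseline does not by itself cure the bias. It left −0.05 to −0.07 SD under independence in B, and in A it moved exchangeable GEE slightly further from the truth.

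What the reply does not answer is the loss of precision, which needs no assumption about drop-out, or the fact that a method valid under a weaker assumption can use the same data.

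**Conclusion.** The point holds as an improvement to a stated method, not as an error that invalidates the plan. The omission of the pre-teaching score from 13.3 and from both regressions in 13.4 is certain, and its cost is a loss of precision under any drop-out pattern. The variance reduction forgone is 17% to 36% against raw scores and 20% to 30% against change scores, for assumed correlations of 0.41 to 0.6.

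The bias is only possible. It runs from near zero to about 0.10-0.12 SD in either direction. The upper end needs both an independence working correlation on raw scores and score-driven loss in one arm only. The documents do not support reading 40% of the planned effect as an expected bias.

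The correlations, the drop-out rules and the placing of the effect at month 12 are assumptions, and the slope of the drop-out rule in simulation A is not reported. The likelihood model was unbiased within simulation error under score-driven loss in both simulations. It would not protect against loss that depends on unobserved answers.

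**What to change.** - **Free improvement.** Add the pre-teaching score of the outcome being analysed to the covariate list in 13.3, and to both the linear regression and the longitudinal bullets of 13.4. The data are already collected on every enrolled student.
- **Cheap improvement.** Estimate the arm difference at each post-teaching survey from a likelihood-based repeated-measures model. Include arm, survey as a categorical factor, arm-by-survey, pre-teaching score and the listed covariates, with unstructured within-student covariance. Use every randomised student who has any post-teaching survey.
- Keep GEE, if wanted, as a sensitivity analysis.

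The cost is a change of wording and one standard model call in Stata. Visits, questionnaire and sample size do not change. The small downside of the likelihood model is its reliance on a specified covariance and approximate normality, which is minor for a behaviour score with a 28-point range (10 to 38) in 600 students.
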